#### Evaluation and credentialing

Upon completion of the training modules, the HEs were evaluated on their mastery of each content area. Written tests were administered, and each HE was observed while conducting mock interviews in both English and Spanish. Performance was scored using a highly customized observational checklist that included each task the HE was required to complete, from the initial greeting of a participant through screening, consent, assessment, and intervention. After successful completion of the tests and mock interviews, the HEs began participant recruitment.

### Interventions

The Life Shift drug intervention and the Shift Gears driving/traffic safety intervention were manual-driven, designed to be of the same duration (10–30 minutes), and available in English and Spanish. Both interventions had core SBI elements that all participants received as well as adaptive elements that allowed the HE to tailor the program based on the patient’s needs and risk level. Both interventions began with the HE providing the participant’s risk level in a nonjudgmental manner using a brochure to help communicate the short- and long-term health, social, and legal effects. For the Life Shift intervention, drug-specific brochures were used when marijuana, cocaine, and methamphetamine were the drugs of choice; otherwise, a general drug use brochure was used. For the Shift Gears intervention, a single brochure was used that focused on issues such as nonattention, road rage, and texting while driving. The patient’s motivation or readiness to change was then assessed using a four-point scale. The readiness information was used to guide additional discussion about the patient’s drug use (or risky driving/traffic behaviors). If the participant was ready to change, the HE discussed possible behavioral changes the patient could incorporate into his/her life. If the participant was not ready to change, the HE helped the patient weigh the pros and cons of his or her present behavior and the pros and cons of change. Together, the HE and participant made a plan specific to the participant based on the discussion and recorded ideas on the worksheet on the back of the brochure.

### Participant recruitment and follow-up

Participant recruitment was conducted from April 2010 through June 2011, with a total of 700 subjects enrolled. Modifications to the experimental protocol were minimal. Figure 1 presents a CONSORT diagram of the flow of patients through the trial. Over 18,000 patients were approached and screened for their eligibility and interest in participating. The great majority of those excluded did not meet the eligibility criteria (e.g., their alcohol use risk exceeded their drug use risk). Of those who were eligible to participate, 29% were excluded, with 9.5% refusing and 19.5% excluded for other reasons (e.g., being interrupted for a medical procedure, becoming too sick or too sleepy to continue). The six-month follow-up rate was 43% with no difference in reasons for loss by condition.

**Figure 1 F1:**
[figure not shown]
CONSORT diagram showing the flow of patients through the trial.

### Outcome measures and analyses

Mixed model analysis of variance (ANOVA) procedures within a general linear model framework will be conducted on the key self-reported outcomes measured by the ASI-Lite. The ASI-Lite composite scores of recent drug use and related medical problems, psychiatric problems, and alcohol use will be analyzed along with health-care utilization outcomes to assess differential change by condition. Because of potential bias introduced by a less-than-ideal response rate, two sets of analyses for the self-reported data will be conducted: complete-case analyses of 294 participants with longitudinal data and intention-to-treat analyses using multiple-imputation data to deal with loss to follow-up (N = 700). With multiple imputation, missing follow-up values are replaced by a series of plausible values rather than by a single value [27-30]. For each outcome, we will use multiple imputation with a chained equation approach to create five imputed data sets and pool these results. Imputed outcome values will be predicted from baseline drug and alcohol use variables, gender, age, income, and drug avoidance self-efficacy. In addition to changes in composite scores, the ASI-Lite drug use scores will be dichotomized into a past 30-day drug use abstinence variable (yes/no) measured at the six-month follow-up. Results of hair analysis will be used to verify abstinence reports. When hair analysis is positive for drug use and self-report is negative for drug use, the participant will be considered nonabstinent.

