## Methods

### Design and procedures

Life Shift/Shift Gears is a NIDA-funded study to evaluate the effectiveness of SBI for drug use among patients visiting large urban emergency departments/trauma units for various reasons not necessarily related to illicit drug use. A randomized, two-group, repeated measures design is being used in which drug-related outcomes of an intervention group will be compared with those of an attention-placebo control group.

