
If an individual screened eligible and consented, he or she was then randomly assigned to one of two conditions. The intervention group (Life Shift) received SBI drug intervention matched to their DAST risk level and drug of choice as identified by participant self-report. To assess the “true” effect of the SBI intervention (i.e., minus the effects of attention), a control group received the same quantity of intervention in the area of driving and traffic safety (Shift Gears) that did not focus on drugged driving. Baseline and six-month follow-up measures were collected for all participants and included standardized subjective drug use measures from the Addiction Severity Index-Lite (ASI-Lite) [11] and other measures presumed to be targeted by the intervention (e.g., functional status, self-efficacy). At face-to-face follow-up conducted by separate measurement technicians, a hair sample in a length corresponding to past-month exposure was tested for the presence or absence of four major categories of illicit drugs (i.e., amphetamines and other psycho-stimulants, cocaine and its metabolites, opiates, and cannabinoids) to increase the accuracy of subjective abstinence reports. In addition, driving and traffic-safety control items were collected to test the result of the experimental manipulation, with the attention-placebo control group expected to have greater pre/post change on these measures than the SBI intervention group.

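### With two waves, the planned mixed ANOVA is a change-score test; regressing six-month scores on condition and baseline is more precise from the same data

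*Protocol article*

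**What the plan says.** The Protocol article, Design and procedures, describes the trial so: "A randomized, two-group, repeated measures design is being used". The same section gives the measurement times: "Baseline and six-month follow-up measures were collected for all participants". No other outcome wave is mentioned.

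Outcome measures and analyses names the model for the main self-reported ASI-Lite outcomes, "Mixed model analysis of variance (ANOVA) procedures within a general linear model framework will be conducted", and the target of the comparison: the composites "will be analyzed along with health-care utilization outcomes to assess differential change by condition". No baseline covariate is named for the outcome model. Baseline variables appear there only as predictors of missing follow-up values.

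The self-reported outcomes are to be analysed twice: "complete-case analyses of 294 participants with longitudinal data and intention-to-treat analyses using multiple-imputation data to deal with loss to follow-up (N = 700"). For the second analysis, "we will use multiple imputation with a chained equation approach to create five imputed data sets and pool these results".

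**The concern.** When there is one measurement before and one after randomization, a repeated-measures model gains nothing from its repeated structure. Its interaction term compares mean change between arms, which fixes the coefficient on baseline at 1. In a randomized trial that coefficient can instead be estimated. The estimated version has a variance that is never larger in large samples, and it is smaller unless the true slope of follow-up on baseline happens to equal 1.

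Precision is scarce here. Only 294 of 700 participants have longitudinal data and recruitment is closed, so lost information cannot be recovered with more patients. The baseline values are already in hand.

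A second, conditional consequence follows. If the arms happen to differ at baseline on a composite, the change-score estimate moves away from the true effect by a predictable amount, and baseline adjustment removes that shift.

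**Working it through.** **Inputs.** From the article: two waves; 294 complete cases; 346 and 354 randomized; five imputations. Not in the article, so assumed: correlation ρ between baseline and six months of 0.3, 0.5 or 0.7; equal SDs at the two waves (SD = 1); two-sided 5% test; completers split in proportion to allocation, 145 and 149. The article gives no power calculation for these outcomes, so there is no figure of its own to reproduce first.

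**1. Is the planned test a change-score test?** On one simulated two-wave data set of 294, the split-plot condition-by-time F, the squared t on change scores and the squared z of a random-intercept model were all 2.3342, with the same estimate (−0.168). The identity holds. On those data the standard error was 0.110 for change and 0.097 with baseline adjustment.

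**2. Relative precision, complete cases.** With SD = 1:

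- variance of change = 2(1 − ρ)
- residual variance after baseline adjustment = 1 − ρ²
- variance ratio = (1 − ρ²) / [2(1 − ρ)] = (1 + ρ)/2
- ratio of standard errors = √[(1 + ρ)/2]
- detectable difference at 80% power = 2.80 × √(variance) × √(4/294), where √(4/294) = 0.1166

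| ρ | SE ratio | SE reduction | Detectable, change score | Detectable, adjusted | Completers a change-score test needs to match 294 adjusted |
|---|---|---|---|---|---|
| 0.3 | 0.81 | 19% | 2.80 × 1.183 × 0.1166 = 0.39 | 2.80 × 0.954 × 0.1166 = 0.31 | 294/0.65 = 452 |
| 0.5 | 0.87 | 13% | 2.80 × 1.000 × 0.1166 = 0.33 | 2.80 × 0.866 × 0.1166 = 0.28 | 294/0.75 = 392 |
| 0.7 | 0.92 | 8% | 2.80 × 0.775 × 0.1166 = 0.25 | 2.80 × 0.714 × 0.1166 = 0.23 | 294/0.85 = 346 |

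In 4,000 simulated trials per setting, the observed ratios of the estimates' SDs were 0.83, 0.87 and 0.93. At ρ = 0.8 the variance ratio is 0.90, so the gain is small from there upward.

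**3. Unequal SDs.** If q is the follow-up SD divided by the baseline SD, the variance ratio is q²(1 − ρ²)/(1 + q² − 2ρq). The denominator minus the numerator is (1 − ρq)², which is never negative. The direction therefore does not depend on the assumptions, but the size does: for q from 0.5 to 1.5 and ρ from 0.3 to 0.7 the ratio ran from 0.23 to 0.998.

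**4. Chance baseline difference.** With equal SDs and a baseline difference d between arms, follow-up means are expected to differ by the effect plus ρd. The change-score estimate is then expected to be the effect − (1 − ρ)d. A one-standard-error difference among completers is √(1/145 + 1/149) = 0.117 SD, giving a shift of 0.082, 0.058 or 0.035 SD at ρ = 0.3, 0.5, 0.7.

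**5. Multiple imputation.** Simulated with N = 700, 294 observed at random, five imputations, and condition and baseline both in the imputation model. Pooled standard errors, change score against adjusted: 0.127 and 0.115 (ρ = 0.3), 0.111 and 0.105 (0.5), 0.090 and 0.087 (0.7). The ratios of the unrounded values are 0.91, 0.94 and 0.97, or reductions of about 9%, 6% and 3%. The gain is smaller because the 406 imputed values already follow a fitted regression on baseline.

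**The case against.** The strongest reply is that this is a choice between two valid methods. The planned test is unbiased over repeated randomizations and nothing else in the article contradicts it. That stands: the point is lost precision, not an error of validity.

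A reader might infer more, namely that chance imbalance will bias the result or is already doing so. The documents do not support this. The shift in step 4 applies only given an actual difference on the outcome concerned. Table 1 gives no ASI-Lite composite by arm and does not describe completers. What it does show is mixed: the at-risk DAST category is 55.0% against 55.2%, while past-month marijuana use is 87.5% against 81.4%.

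It is also fair to object that the larger percentages belong to the complete-case analysis alone, and that every figure rests on an assumed correlation and equal SDs. Both objections stand. The smaller imputation figures further assume condition is among the imputation predictors, and the article's list does not name it.

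A condensed article may leave model terms to a fuller document. A mixed model constraining baseline means to be equal across arms would be about as precise as baseline adjustment. Nothing in the section describes one, however, and an ANOVA in a general linear model aimed at differential change reads most naturally as the ordinary form.

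Finally, recruitment ended in June 2011 and the follow-up rate is already reported, so a change of main model now needs a documented justification. That affects how the change is made, not whether it is worthwhile.

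**Conclusion.** The point holds as one of efficiency. As described, the main test on each composite is a change-score t-test, and adjusting the six-month value for baseline would be at least as precise in large samples whatever the correlation or SDs. The direction is secure. The size is not, because the article supplies neither quantity: the gain is material in the complete cases at low to moderate correlation, modest under multiple imputation, and close to nil if the slope on baseline is near 1.

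The planned analysis remains valid. The six-month abstinence outcome is outside this point. The variance formulas describe continuous scores; for utilization outcomes the same adjustment is sensible, but these percentages should not be carried over to them. With 294 of 700 followed up and the outcome analysis unfinished according to the Abstract, the change should be made.

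**What to change.** In Outcome measures and analyses, for each ASI-Lite composite and each utilization outcome measured at both waves, make the main model the six-month value regressed on condition and that outcome's own baseline value. Apply it to both the complete-case and the imputed data, and include condition in the imputation model. Keep the condition-by-time ANOVA as a sensitivity analysis. Hospital and DAST risk category may be added as covariates, but nothing in this point requires them.

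The text change is a sentence or two and needs no new data. The other cost is procedural: a dated record of the change and its reason, made before anyone compares outcomes by arm.

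### As written, the imputation model omits randomised condition, so the intention-to-treat estimate is expected to shrink to about 0.42 of the true effect if those lost would have responded like completers

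*Protocol article*

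**What the plan says.** All the relevant text is in the protocol article, mainly under Outcome measures and analyses.

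- Purpose of the analysis: the ASI-Lite composites and health-care utilization are analysed "to assess differential change by condition".
- Two analysis sets for the self-reported data: "complete-case analyses of 294 participants with longitudinal data and intention-to-treat analyses using multiple-imputation data to deal with loss to follow-up (N = 700").
- Method: "we will use multiple imputation with a chained equation approach to create five imputed data sets and pool these results", done for each outcome.
- Predictors: "Imputed outcome values will be predicted from baseline drug and alcohol use variables, gender, age, income, and drug avoidance self-efficacy".
- Outcomes beyond drug use: "related medical problems, psychiatric problems, and alcohol use will be analyzed along with health-care utilization outcomes".

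Participant recruitment and follow-up adds: "The six-month follow-up rate was 43% with no difference in reasons for loss by condition". Limitations promises an attrition analysis and outcome analyses that adjust for missing data, but adds nothing to the predictor list. No section says that imputation is run separately in the two arms.

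**The concern.** An imputation model should contain every term whose effect the analysis will estimate. Here the analysis estimates the effect of condition on change, and condition is missing from the stated model. Missing follow-up values in both arms are then drawn from one common regression on baseline variables. Randomisation makes those variables unrelated to condition in expectation, so the imputed part of the data shows, on average, no arm difference whatever the truth. Chained equations would not restore it: a participant lost at six months has no observed follow-up measure through which the effect could enter.

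Imputation was introduced to protect the result against bias from attrition. As written, it adds a bias towards no effect in the analysis labelled intention-to-treat. A gap between that result and the complete-case result could then be mistaken for evidence of attrition bias.

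A smaller, related gap is that the listed clinical predictors cover drug and alcohol use only. Imputed medical, psychiatric and utilization values are therefore not tied directly to their own baselines, although change from baseline is what is tested.

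**Working it through.** **Inputs from the article.** 294 participants with longitudinal data; N = 700; arms of 346 (Life Shift) and 354 (Shift Gears) from Table 1; five imputations; stated follow-up of 43%.

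**Inputs assumed.** Completers per arm are not in the available text (the flow diagram is not shown): near-equal 147/147, with a range of 119/175 to 175/119. Effect size, baseline correlation and significance level are not stated: 0.30 SD, 0.3 to 0.6, and two-sided 5%.

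**Step 1, the article's own figure.** 294/700 = 42.0%. The stated 43% would be 0.43 × 700 = 301, a difference of 7 participants that does not matter here. Imputed: 700 − 294 = 406, or 58.0%.

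**Step 2, expected attenuation.** Let f1 and f0 be the follow-up fractions in the two arms, w the share of completers who are in arm 1, and δ the true effect, the same in completers and those lost. Imputation that ignores condition gives the missing in both arms the mean μ0 + wδ. Then:

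- Arm 1 mean = μ0 + δ[f1 + (1 − f1)w]
- Arm 0 mean = μ0 + δ(1 − f0)w
- Difference = δ[f1(1 − w) + f0·w]

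With 147/147: f1 = 147/346 = 0.425, f0 = 147/354 = 0.415, w = 0.5, so the factor is 0.420. With 175/119: f1 = 0.506, f0 = 0.336, w = 0.595, so the factor is 0.506 × 0.405 + 0.336 × 0.595 = 0.405. The 119/175 split also gives 0.405. Using 43% follow-up gives about 0.43.

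**Step 3, simulation.** 346 + 354 participants with about 42% observed; five proper normal imputations; Rubin's rules; arm difference in change scores, which equals the condition-by-time term with two time points; data missing completely at random, or at random given baseline; 1,500 runs per setting. True effect 0.30 SD:

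| Baseline correlation | Imputation model | Estimate ÷ truth | Empirical SD | Mean pooled SE | Power |
|---|---|---|---|---|---|
| 0.3 | as listed | 0.41–0.42 | 0.075–0.076 | 0.108–0.109 | 11–13% |
| 0.3 | condition added | 0.99 | 0.127–0.129 | 0.127–0.128 | 57% |
| 0.6 | as listed | 0.41–0.42 | 0.054 | 0.085 | 20–21% |
| 0.6 | condition added | 1.00 | 0.102–0.103 | 0.102–0.103 | 75% |

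Across assumed effects of 0.2, 0.3 and 0.4 SD, the factor is 0.413 to 0.430 as listed and 0.98 to 1.01 with condition added. The complete-case analysis in the same runs recovers 0.98 to 1.03.

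At 0.30 SD, coverage of the 95% interval is about 70% at correlation 0.3 and about 50% at 0.6 (50–72% over the runs made), against about 95% with condition added. With no true effect, the listed model rejects less than 1% of the time instead of about 5%.

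**Step 4, more imputations.** At 0.30 SD and correlation 0.5, the mean estimate without condition is 0.126 with five imputations and 0.127 with 60. The bias comes from the model, not from the number of imputations.

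**The case against.** The strongest reply is that this is a condensed article. The predictor sentence does not say that only these variables are used. It may list the auxiliary covariates, with condition included, or imputation run by arm, in a fuller plan that is not available. That stands as a limit: a reader might infer that condition was definitely left out of the analysis, and the article does not establish this. It does not remove the point. The article prints a specific list, and that list, followed as it stands, does not suit the stated test.

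Second, the 0.42 needs a similar effect in those lost. Limitations says that participants who were incarcerated or in inpatient treatment could not be followed, and that attrition bias is still to be tested. If the effect in those lost were k times that in completers, the estimate relative to the true effect over all 700 would be 0.42/(0.42 + 0.58k): 0.42 at k = 1, 0.42/0.71 = 0.59 at k = 0.5, and 1 at k = 0. This objection stands, so the factor must carry its condition. Also, the zero arm difference among imputed values is an expectation; chance baseline imbalance can move it in a single data set.

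Third, a reader might infer that a working intervention would probably be declared ineffective. The article does not support that. The complete-case analysis is planned alongside and is unaffected, and no rule makes the imputed result decisive. Imputation is also tied to the self-reported data, so the point should not be stretched to the hair-verified abstinence outcome, which the article does not say will be imputed.

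Fourth, power and coverage rest on an assumed effect and correlation, so they are given as ranges. Under the equal-effect condition, the attenuation factor hardly depends on them.

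**Conclusion.** The point holds for the model as written. Using only the listed baseline predictors, the intention-to-treat estimate of differential change is biased towards zero, with an expected factor of about 0.42 (0.40 to 0.43 over plausible follow-up splits and the two stated follow-up figures). This assumes data missing at random and a similar effect in those lost. The pooled standard error exceeds the true sampling variability (about 0.108 against 0.075 at correlation 0.3), so power falls further and the test almost never rejects when there is no effect.

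The missing baseline values for the medical, psychiatric and utilization outcomes are a secondary weakness whose size was not estimated. For drug and alcohol outcomes, the listed variables plausibly supply the baseline.

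**What to change.** State that randomised condition enters every imputation equation, or that imputation is run separately within each arm. Add to each equation the baseline value of the outcome being imputed, for the medical, psychiatric and utilization outcomes as well as drug and alcohol use. If the full plan already does this, one sentence saying so settles the matter.

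Condition-by-severity terms, hospital or patient-location predictors and predictive mean matching are optional; nothing in the article requires them.

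The cost is a sentence of wording and a few lines of code, with no new data. The abstract says outcome analysis is not yet complete, so the change can still be made before results are reported.

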#### Module 3: mental health

Data from CASBIRT indicated that co-occurring mental health disorders were common among illicit drug users who use emergency and trauma services at urban San Diego hospitals. To understand how to best work with this patient population, the mental health training curriculum began with overviews of the mental illnesses HEs were most likely to encounter: Axis I disorders, including mood, anxiety, and psychotic disorders; Axis II personality disorders; and co-occurring disorders, since many patients who use illicit drugs simultaneously suffer from mental health challenges [24]. Prominent signs and symptoms were explained to help the HEs identify these disorders based on the behaviors and affect of prospective participants. The mental health module was designed in part to reduce HE anxiety about working with these patients while simultaneously decreasing stigma, which is an ongoing challenge for people living with mental illness [25]. There was also a section dispelling the connection between violence and mental illness, a popular cultural misconception with minimal basis in reality [26].

The most critical element of the mental health module was discussion of which types of patients were suitable for enrollment. It was essential that the HEs be able to apply critical thinking skills when recruiting mildly symptomatic individuals into the study. Since inclusion criteria only required that a participant be awake, alert, and able to engage in the interview, patients with mild to moderate mental health challenges often met these criteria and were considered appropriate to be invited to participate. Patients who were floridly psychotic or otherwise symptomatic to the point of distraction were not considered eligible for participation.

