Other process measures were collected as part of the participant interview process and recorded in the data collection instrument. Such variables included the hospital location and whether the participant was an emergency or trauma patient. This knowledge helped illuminate which locations and departments were the most fruitful for recruitment and which environments were best suited for administering SBI. Start time and end times of each intervention were also recorded, which served a dual purpose. First, it identified peak recruitment times, which was helpful for scheduling purposes. Second, it allowed project management to monitor the time HEs spent delivering the intervention. From a quality assurance perspective, it was critical to monitor the time of the brief interventions to ensure they were lasting the intended amount of time and that both the experimental and control groups received interventions of the same average duration.

Quality assurance was the responsibility of the project manager, who possessed a Master of Social Work with a concentration in administration, undergraduate education and experience in chemical dependency counseling, and multiple years of experience as a project manager. Drawing on this background, the project manager shadowed the HEs as they conducted participant enrollment interviews and, utilizing the observational checklist, was able to reinforce effective techniques and offer immediate feedback about areas in need of improvement. While the HEs’ performance generally met or exceeded expectations, there were rare instances in which the project manager observed drift from the experimental design. Most commonly, this occurred when a HE missed an opportunity to delve further into a participant’s behaviors and uncover motivation to change.

To mitigate the natural process of drift from the experimental design, the HEs remained engaged in ongoing training activities for the duration of the recruitment period. They met with the project manager on a regular basis and continued to engage in didactic and experiential MI training. They were also treated as a valuable project resource; when areas in need of improvement were identified, the HEs were actively solicited for feedback and suggestions on what could be done differently. By approaching the HEs in this collaborative manner, the project benefited from their insights while simultaneously strengthening their engagement in their respective roles.

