### Limitations

Due to its pragmatic nature, this study is primarily a test of effectiveness, but the attention-placebo control group has the characteristics of an efficacy trial. One of the challenges in hiring and training personnel was to simultaneously prepare them for a randomized controlled trial and a real-world SBI. As a result, there are limitations to transportability. Most notably, the training period for HEs was a full month, probably longer than can realistically be expected for service programs. However, a large portion of the training was dedicated to research concepts, which accounts for most of the disparity between the training duration of this study and what practitioners could reasonably accommodate. The other issues of transportability are related to funding and the ongoing question of whether SBI services should be delivered by paraprofessionals or trained medical staff. Enthusiasm for SBI services has been building in California in recent years, and the CASBIRT health educator model, upon which this study was built, has been recognized as a realistic alternative in health-care settings where medical personnel are unavailable [34]. Similarly, Bernstein and colleagues [5] found that, regardless of setting, SBI programs tend to migrate to the use of HEs over medical professionals. They also found that, although SBI funding is not guaranteed, as the model continues to result in cost savings, and as new billing codes are activated, it becomes increasingly likely that there will be funds to support these positions.

Although the HEs in this study were successful in their recruitment efforts, and despite concerted cohort maintenance efforts, a considerable number of participants were lost to follow-up, a common problem in studies of drug users [35,36]. Project staff aggressively followed up with participants by phone and mail and made home visits when it was feasible and safe. Study design did not allow for follow-up with participants who were incarcerated or enrolled in inpatient treatment; if it had, it is possible that the follow-up rate would have been higher. A low follow-up rate is of concern because of potential threats to validity, especially to the degree that the characteristics of those lost to follow-up differ by experimental condition. We plan to conduct a thorough analysis to test attrition bias and to conduct outcome analyses that adjust for missing data.

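### The imputation predictors leave out measured baseline variables, including the psychiatric and medical outcomes' own baselines, and are not tied to the planned attrition analysis

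*Protocol article*

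**What the plan says.** Two analyses of the self-reported outcomes are planned: "complete-case analyses of 294 participants with longitudinal data", and an intention-to-treat analysis of all 700 by multiple imputation. Chained equations are to be used for each outcome, to "create five imputed data sets and pool these results". The predictors are then named: "Imputed outcome values will be predicted from baseline drug and alcohol use variables, gender, age, income, and drug avoidance self-efficacy". The sentence has no open-ended wording and applies to every imputed outcome. Besides drug use, these include the medical, psychiatric and alcohol composites and health-care utilization.

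Other baseline information was collected. Under Process measurements the article says of data recorded at the participant interview: "Such variables included the hospital location and whether the participant was an emergency or trauma patient". Table 1 reports race/ethnicity and patient location. Change in the psychiatric and medical composites is to be compared by condition, which requires baseline values.

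On loss, Participant recruitment and follow-up states: "The six-month follow-up rate was 43% with no difference in reasons for loss by condition". Limitations adds: "We plan to conduct a thorough analysis to test attrition bias and to conduct outcome analyses that adjust for missing data". No sentence says that the attrition result will determine which variables enter the imputation.

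**The concern.** Multiple imputation removes only the attrition bias that its predictors explain. If a measured variable predicts both who is found at six months and how they are doing, omitting it leaves avoidable bias in the imputed values. The N = 700 analysis is the planned answer to losing more than half of the participants, so the choice of predictors carries much of its credibility.

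Two things stand out. First, the composites analysed for change include outcomes whose own baseline is not among the predictors, although that is usually the strongest single predictor available. Second, the attrition analysis may show that an unlisted variable is related to loss, and the article does not say what would then happen to the imputation model.

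**Working it through.** **Amount missing.** Enrolment: "with a total of 700 subjects enrolled". Complete cases: 294. So 294/700 = 42.0% observed and 700 − 294 = 406 missing (58.0%). The stated 43% corresponds to 0.43 × 700 = 301 people (298 to 304 with rounding). A few people followed up without usable longitudinal data would explain the gap, and nothing below depends on it.

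**Outcomes imputed without their own baseline.** Take the limiting case in which the listed variables carry no information on baseline psychiatric status and loss is unrelated to it. Imputed follow-up values are then uncorrelated with their own baseline. Only the observed 42% contribute, so the baseline-to-follow-up covariance in the completed data is 0.42 of its true value. The listed variables will carry some of this information, so the real attenuation is smaller. The result is lost precision in a change analysis and, if baseline status also predicts loss, biased arm means.

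**Bias in the arm difference from an omitted factor.** The documents give no effect of any variable on loss, so these inputs are assumptions:
- a binary factor unrelated to the listed predictors, worth 0.3 to 0.8 SD on the outcome;
- overall follow-up of 42%;
- retention with the factor of 42% v 30% by arm, or 46% v 26% (average 36% in both cases);
- retention without the factor equal in both arms;
- condition included in the imputation model. The list does not name it; that is a separate matter.

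With factor prevalence p, the retained proportion without the factor is 0.42 − 0.36p in each arm: 0.294 for p = 0.35, and 0.3606 for p = 0.165 (trauma location, Table 1). The factor's share among the retained is p × retention / (p × retention + that proportion). Randomisation balances the factor at baseline, so bias = difference in shares × effect.

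| p | Retention | Shares among retained | Difference | Bias (SD) |
|---|---|---|---|---|
| 0.35 | 42 v 30% | 0.147/0.441 = 33.3% v 0.105/0.399 = 26.3% | 0.070 | 0.021 to 0.056 |
| 0.35 | 46 v 26% | 0.161/0.455 = 35.4% v 0.091/0.385 = 23.6% | 0.117 | 0.035 to 0.094 |
| 0.165 | 42 v 30% | 0.0693/0.4299 = 16.1% v 0.0495/0.4101 = 12.1% | 0.040 | 0.012 to 0.032 |
| 0.165 | 46 v 26% | 0.0759/0.4365 = 17.4% v 0.0429/0.4035 = 10.6% | 0.068 | 0.020 to 0.054 |

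With the 294 split evenly (147 per arm, assumed), the unadjusted SE is √(2/147) = 0.117 SD. The largest bias is 0.094/0.117, about 0.8 SE; at the trauma prevalence it is 0.054/0.117, about 0.46 SE.

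**When the bias appears.** A simulation used 346 v 354 participants, five imputations, about 42% observed and 1,500 replicates. It assumed a true difference of −0.30 and an omitted continuous factor with outcome slope 0.4 and log-odds of being observed 0.8 per SD, with condition in the model.
- Factor acts on loss equally in both arms: difference −0.298 without it and −0.300 with it. The overall mean is +0.017 without it, against a true −0.148, and −0.149 with it.
- Factor acts on loss in one arm only: difference −0.136 without it and −0.300 with it.

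The second case is a deliberately strong contrast. Its bias, 0.300 − 0.136 = 0.164, exceeds one SE and shows how far the size depends on the inputs.

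**The case against.** The case against has real force.

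- **A condensed article.** How an attrition analysis guides the choice of auxiliary variables is often left to a fuller document. A reader might infer that the attrition result cannot reach the imputation model. The article does not support that: it promises both steps in one sentence and bars no addition. What stands is that the predictor list itself is stated, so its content can be judged.
- **No evidence that these variables drive loss.** A reader might take them as likely causes of the 58%. No passage shows this. The remark that "co-occurring mental health disorders were common among illicit drug users who use emergency and trauma services" rests on data from another programme and concerns prevalence, not attrition. The only obstacles to follow-up that the article names, incarceration and inpatient treatment, arise after baseline, and none of the omitted variables measures them.
- **No shown imbalance by arm.** Reasons for loss are reported as not differing by condition. That is not a comparison of participant characteristics, but it is the only evidence in the text and it points away from the harmful case. There is a possible route to arm-dependent loss: treatment referral was offered to higher-risk intervention participants (Module 2), and people in inpatient treatment could not be followed (Limitations). That route runs through drug-use severity, which the list already covers, so it does not show the omitted variables acting this way. The 46% v 26% scenario at 35% prevalence also implies overall follow-up of 45.5% v 38.5%, which the text does not report (the CONSORT figure is not shown).
- **The list is partly a category.** AUDIT and DAST-10 plausibly fall under baseline drug and alcohol use, so they should not be called omitted.
- **Data-driven remedies.** Adding whatever proves associated with loss, without a threshold, would shape the model after the fact. This is correct, and the fix below avoids it.

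**Conclusion.** The concern holds in a limited form. One predictor list serves all imputed outcomes, measured variables that could matter are not on it, and it is not linked to the attrition analysis. The omission of the psychiatric and medical baselines is the firmest part, because it is a weakness whatever drives loss.

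A biased treatment effect is not established. It requires an omitted variable that predicts the outcome beyond the listed ones and affects loss differently by arm. Under the moderate assumed inputs the bias is about 0.02 to 0.09 SD at 35% prevalence, below one SE of 0.117 SD, and smaller at the trauma prevalence. Only the stronger assumed contrast exceeds one SE. If loss acts equally in both arms, the arm difference is essentially unaffected, and arm-level means and precision suffer instead.

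**What to change.** Before outcome analysis, pre-specify the imputation set as:
- the variables already listed, confirming that AUDIT and DAST-10 scores are among the drug and alcohol use variables;
- hospital, emergency versus trauma location, and race/ethnicity;
- the baseline value of each outcome imputed, including the psychiatric and medical composites.

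State that baseline variables which the attrition analysis associates with loss, by a criterion fixed in advance, will be added. Keep variable-by-condition terms for a sensitivity analysis.

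No new data collection is called for. The cost is a sentence or two in the plan, slightly more modelling work, and some added imputation variance from fitting a larger model to 294 observed outcomes.
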